# STUDY DESIGN

## Overall Design

This is multicenter phase 2, single group assignment, open-label dose-escalation, pharmacokinetic trial. A traditional 3+3 dose-finding design was not practical as all participants would not receive the lowest cannabinoid dose and the recommended “start low and go slow” approach to titration. The trial will be conducted across three centres in Canada and was designed in collaboration with youth from the KidsCAN Young Persons’ Advisory Group (YPAG) and the Solutions for Kids in Pain (SKIP) network. The Canadian Childhood Cannabinoid Clinical Trials Parent Advisory Committee provided insight on the outcome measurement tools and the consent form. Three youth advisors with chronic migraines have been involved throughout the study design process and will advise on recruitment strategies, reporting and dissemination as steering committee members. The youth engagement plan, findings and evaluation are described elsewhere (*publication under review)*. The research team held three virtual meetings with youth advisors to discuss which outcomes are important to youth, and decided on data collection methods and tools. The research team also co-designed the recruitment materials, including consent forms, with youth advisors. The PI will send safety reports annually to Health Canada as a Clinical Trial Notification to strengthen the evidence base of product specific cannabis data. The study will consist of three different phases: baseline (1 month), followed by escalating treatments monthly. Participants will wean in the same dosing increments over 4 weeks and will complete a pre and post study questionnaire.

**Baseline Run-In Phase (from visit 1 to visit 2, the first month)**

Eligible adolescents will be asked by their healthcare providers if they are interested in learning more about this research study. A study team member, who is not involved in patients’ care, will present the study, consent documents and answer any questions from the patients and their families. Participants who meet the inclusion criteria and sign the informed consent (ICF) will be enrolled in the study.

Upon enrollment, baseline visit (visit 1) will be scheduled to collect participant’s demographic data, medical history and concomitant medicine history (in the past 2 years). In addition, an electronic headache diary will be set up for participant via REDCap.

C4T Baseline Safety Screening Tool for Cannabis-related interventional trials, also called SCR Checklist, will be used at visit 1 to capture thorough medical history, along with respective CTCAE grade level to document medical condition severity level at baseline. Medical conditions reported as medical history at baseline should not be reported as AE during the study, unless increases in frequency or severity. For instance: only fatigue increased in severity compared with baseline level should be reported as AE from baseline onwards.

Moreover, the baseline values (collected at visit 1) of each experimental measure will be estimated prior to administering the intervention/study product to the participants on visit 2. The participant will be asked to maintain the electronic headache diary, reporting headache-free days encountered by the participants, and will be asked to fill the following age validated scales (described above) on sleep related impairment, mood, and life impact. Participants will select three goals and work through goal attainment scaling each visit.

A handout on cannabis oil administration will be co-created with the youth advisors and will be provided to all study participants and their families. There will also be a demonstration by the research coordinator at the first study visit. On visit 1, the blood sample will be drawn from the study participants to measure the plasma concentration of CBD, THC and its metabolites and saliva sample for extraction of genomic DNA to allow for genotyping of pharmacogenetic variants. ECG (within 3 months of screening or at screening) will be recorded for all the participants to ensure participants do not have any concerning changes in cardiac electrical activity. All participants will undergo the lab investigation for liver transaminases (ALT/AST) and creatinine levels for all follow-up visits. All the study participants will be provided with an option of using wrist-worn device (optional) for actigraphy to monitor their sleep parameters. Participant will be advised that if they choose to accept and wearing the actigraphy device, data generated on the device won’t be collected or analyzed for study purpose.

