## Schedule of Activities (SoA)

**Table 1.** CAN-CHA schedule of activities

| Study visit # | **1**  (Baseline) | **2** | **3** | **4** | **5** | **6** | **7** |
| --- | --- | --- | --- | --- | --- | --- | --- |
| Day # | **1** | **30** | **60** | **90** | **120** | **150** | **180** |
| Follow up window (days) | **±5** | **± 5** | **± 5** | **±5** | **± 5** | **±5** | **± 5** |
| Informed Consent | X |  |  |  |  |  |  |
| Demographics | X |  |  |  |  |  |  |
| Medical history (safety screening with SCR Checklist)^b^ | X |  |  |  |  |  |  |
| Review ongoing co-existing medical conditions^d^ |  | X | X | X | X | X | X |
| Concomitant medication and therapy review | X | X | X | X | X | X | X |
| IP intervention follow-up^a^ |  | X^a^ | X^a^ | X^a^ | X^a^ | X^a^ |  |
| Intervention dose of CBD (mg/kg/day) |  | 0.2- 0.4 | 0.4-0.6 | 0.6-0.8 | 0.8-1.0 | Wean |  |
| Physical exam | X |  |  |  |  |  | X |
| Vital signs and weight^c^ | X | X | X | X | X | X | X |
| Pregnancy test in females^e^ | X | X | X | X | X | X | X |
| Assign Daily eDiary via REDCap | X |  |  |  |  |  |  |
| Review of Daily Diary |  | X | X | X | X | X | X |
| Review of Adverse Events |  | X | X | X | X | X | X |
| Review of Cannabis-related Adverse Event |  | X | X | X | X | X | X |
| Cannabis Use Disorder Identification Test Short-Form (CUDIT-SF) | X |  |  |  |  |  | X |
| Pediatric Sleep-Related Impairment– Short Form 8a Scale | X | X | X | X | X | X | X |
| PedsQL Family Impact | X | X | X | X | X | X | X |
| Pediatric Short Form v2.0 - Anxiety - 8a scale | X | X | X | X | X | X | X |
| Pediatric Short Form v2.0 - Depressive Symptoms 8a scale | X | X | X | X | X | X | X |
| Pediatric Pain Interference – Short Form 8a scale | X | X | X | X | X | X | X |
| Pediatric Positive Affect – Short Form 8a | X | X | X | X | X | X | X |
| Self-directed goal attainment | X | X | X | X | X | X | X |
| Participant Trial Expectation Survey | X |  |  |  |  |  | X |
| Blood samples (8mLs, approx.) | X | X | X | X | X | X | X |
| Saliva Sample for Pharmacogenomics | X |  |  |  |  |  |  |
| Electrocardiogram (if not done in the last 3 months) | X |  |  |  |  |  |  |
| Drug Accountability |  | X | X | X | X | X | X |
| Visit duration (minutes) | 60 | 45 | 60 | 45 | 60 | 45 | 60 |

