### Dosing and Administration

Eligible study participants will complete a baseline phase (first month) where no investigational product will be administered for one month. At the four subsequent study visits, study participants will receive escalating doses of CBD-enriched CHE from 0.2-0.4 mg/kg/day to 0.8-1 mg/kg/day for four months, with dose increases happening monthly over four months in 0.2mg increments. Participants will self-administer the investigational product orally following a dosing calendar and all dosing calculations will be based on weight at baseline. The product comes as CHE oil, 25% of the daily dose will be administered in the morning, and the remaining 75% of the dose in the afternoon to mimic endogenous cannabinoid diurnal variation. Upon completing the baseline phase, the eligible study participants will receive a supply of study products delivered to their home from the study central pharmacy at Children’s Hospital Research Institute of Manitoba (CHRIM). Each package will include a participant-specific dosing calendar for dose confirmation, and a return envelope to the central study pharmacy at CHRIM for used bottles to be mailed back for destruction and accountability.

During visit 2, study participants will be instructed how to administer the investigational product (IP) at a dose of 0.2-0.4 mg/kg/day divided into two doses (BID, 25% dose in morning and 75% in the afternoon) for one month. Participant’s day 1 of IP dose starts the day after visit 2.

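### The protocol fixes baseline at visit 1, one untreated month before dosing: questionnaire changes absorb that month, and the two diary endpoints cannot be formed there

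*Protocol*

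**What the plan says.** All references are to the Protocol.

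- **Baseline rule.** The Baseline Run-In Phase text under Overall Design states that "the baseline values (collected at visit 1) of each experimental measure will be estimated prior to administering the intervention". Table 1 in the Schedule of Activities also labels visit 1 (day 1) as baseline. Study Intervention Compliance counts follow-up visits from visit 2.
- **A competing definition.** The heading over that same text reads "Baseline Run-In Phase (from visit 1 to visit 2, the first month". Dosing and Administration has participants "complete a baseline phase (first month) where no investigational product will be administered for one month", and the Synopsis also gives baseline as one month.
- **First dose.** Under Dosing and Administration, "day 1 of IP dose starts the day after visit 2".
- **Questionnaires.** Table 1 schedules all the PROMIS forms, PedsQL Family Impact and goal attainment at every visit. The anxiety row, for example, begins "Pediatric Short Form v2.0 - Anxiety - 8a scale | X | X | X".
- **Diary.** The row "Assign Daily eDiary via REDCap | X" is marked at visit 1 only. The row "Review of Daily Diary" is marked from visit 2 onward. The Electronic headache diary section has pain ratings recorded daily starting from visit 1.
- **Use of baseline.** Section 10.3.2 summarises secondary outcomes at each timepoint and reports absolute and percentage change from baseline, with summaries overall and by dosage level. The Electronic headache diary section judges efficacy on headache intensity by its reduction from baseline.

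**The concern.** Visit 2 is the last measurement before any product is taken, yet the text treats it as a follow-up visit and anchors change scores a month earlier. In a single-group, open-label trial, the untreated month is the only internal evidence of what happens without the drug. Participants enter with frequent headache after at least two failed treatments and agree to engage with psychology and physiotherapy, so some change before dosing is plausible. A visit 1 anchor places that change inside each later questionnaire change score, where nothing separates it from a response to the product.

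The diary endpoints have a different problem. A monthly count of headache-free days and an average of daily ratings both need a period of recording, and at visit 1 there has been none. The rule covers each experimental measure, so for these two it cannot be carried out.

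There is also a labelling risk. Table 1 prints the lowest dose range in the visit 2 column, and section 10.3.2 promises summaries by dosage level. Pre-dose visit 2 scores could therefore be tabulated as if observed on the first dose level.

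**Working it through.** There is no stated calculation to reproduce. The protocol has no hypothesis, SD, correlation or power figure, and N = 20 is justified descriptively. The check has three parts.

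**1. Timing (all inputs from Table 1 and Dosing and Administration)**

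Visits fall on days 1, 30, 60, 90, 120, 150 and 180, each ±5 days. First dose is day 30 + 1 = 31.

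- Visit 1 to first dose: 31 − 1 = 30 days. With the windows, the range is (25 + 1) − 6 = 20 to (35 + 1) − (−4) = 40 days.
- Visit 2 to first dose: 1 day.
- Untreated run-in: 30 − 1 = 29 days. Its share of the interval since visit 1:

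| Visit | Days since visit 1 | Untreated share |
|---|---|---|
| 2 | 29 | 29/29 = 100% |
| 3 | 59 | 29/59 = 49% |
| 4 | 89 | 29/89 = 33% |
| 5 | 119 | 29/119 = 24% |
| 6 | 149 | 29/149 = 19% |
| 7 | 179 | 29/179 = 16% |

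The visit 2 change from baseline contains no drug exposure at all.

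**2. Regression to the mean (illustration only; every input is assumed)**

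If a group's visit 1 mean lies k SDs from the population mean and two visits correlate at r, the expected change with an inert drug is (1 − r) × k × SD. Here k is distance from the population mean. A departure from a participant's own usual level would instead be expected to disappear in full.

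With SD = 10, in points:

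| k | r = 0.5 | r = 0.7 | r = 0.9 |
|---|---|---|---|
| 0.5 | 2.5 | 1.5 | 0.5 |
| 1.0 | 5.0 | 3.0 | 1.0 |
| 1.5 | 7.5 | 4.5 | 1.5 |

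A simulation with no drug effect, equal correlation between visits and selection of participants above the mean at visit 1 gave these mean changes to visit 3:

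| r | Visit 1 as baseline | Visit 2 as baseline |
|---|---|---|
| 0.5 | −3.98 | 0.01 |
| 0.7 | −2.38 | 0.01 |
| 0.9 | −0.80 | −0.01 |

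This shows the mechanism and that a visit 2 anchor removes it under these assumptions. It does not estimate the bias in this trial. The simulation selects on the score itself, whereas the Inclusion Criteria select on headache days over more than three months, so regression on PROMIS or PedsQL would be indirect.

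**3. Diary endpoints**

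Completed diary days at visit 1: none, or one if an entry is made that day. By visit 2: about 29. A monthly count therefore has no visit 1 value, and a daily average has at most one rating behind it. If the within-person daily SD is 1.5 to 2.5 and day-to-day autocorrelation is 0 to 0.4 (both assumed), the standard error of one participant's baseline rating is 1.5 to 2.5 from a single day and 0.28 to 0.70 from 29 days.

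**The case against.** Several points on the other side stand.

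- **A reader might infer that every change score is inflated, including the headache endpoints.** The documents do not support that. The protocol repeatedly calls the first month the baseline phase, and the diary runs through it. If that month is used, as is probably intended, run-in change is not counted in headache-free days or average pain intensity. For these two the defect is a contradictory definition.
- **A reader might infer that no pre-dose diary data exist.** Pain ratings start at visit 1, so even a single visit 1 rating may exist, and the run-in month is recorded. What is missing is a statement that this month is the baseline.
- **A reader might infer that the untreated change is thrown away.** Section 10.3.2 summarises each timepoint, and individual data are listed by timepoint, so the visit 1 to visit 2 questionnaire change should be visible. The risk lies in how later changes are read.
- **A visit 2 anchor is not perfectly clean.** Product is shipped before visit 2, so open-label expectation may already colour those self-reports. Psychology and physiotherapy continue during dosing, so no choice of baseline removes their effect.
- **Goal attainment differs.** Goals are chosen in the baseline phase and the scale assigns −2 as its baseline level, so moving its anchor to visit 2 would conflict with the instrument.

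Baseline windows are often left to the analysis plan. Here, though, the protocol states a rule for every measure, and that rule is unworkable for two endpoints and poorly placed for the questionnaires.

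**Conclusion.** The point holds in a limited form. For PROMIS and PedsQL Family Impact, a visit 1 baseline puts about one untreated month (30 days to first dose, 20 to 40 with the visit windows) into every later change score, and without a control arm that part cannot be separated from a drug effect. For headache-free days per month and average daily pain intensity, the visit 1 rule cannot be executed and contradicts the protocol's own run-in baseline phase.

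The timing follows from the protocol alone. The size of any bias does not: the point values in the illustration rest wholly on assumed SD, correlation and selection, and should not be quoted as an estimate. A shift toward apparent benefit is likely but not certain.

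The consequence is a risk of misreading secondary, descriptive summaries. The primary endpoint, adverse events, is not a change score and is unaffected. The correction is still worth making, because these summaries are the trial's evidence on effect and the remedy is cheap.

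**What to change.** In the Baseline Run-In Phase text, delete the visit 1 parenthesis and state the baseline by endpoint:

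- **Headache-free days and average daily pain intensity:** the diary month from visit 1 to visit 2.
- **PROMIS forms and PedsQL Family Impact:** the visit 2 score completed before first dose, with visit 1 used only if visit 2 is missing.
- **Goal attainment:** keep the anchor set when goals are chosen, and show the visit 2 score as pre-dose progress.

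Report the visit 1 to visit 2 questionnaire change separately as untreated change. Do not tabulate visit 2 scores under the first dose level. Summarise later visits by the dose actually taken in the preceding month. A fixed map from visit to dose would mislabel participants who did not move up after a dose-limiting toxicity, and those who stopped product but stayed in follow-up. Adjust the baseline label in Table 1 to match.

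Cost: a few sentences and one table label, with no new data or visits. Reported improvements may shrink, and because product is shipped before visit 2, the visit 2 self-reports may already carry some expectation. Showing visit 1 alongside visit 2 lets the reader judge that.

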**Treatment Phase (visit 2 to visit 5)**

Before visit 2 (start of the second month) the study participants will receive CBD-enriched CHE (MPL-001) and a dosing calendar shipped to their homes before visit 2. Participants will be instructed to administer it at a dose of 0.2-0.4 mg/kg of CBD per day divided into two doses (25% in the morning and 75% in the afternoon after school). Participant-specific dose will be prescribed by site investigator. Participants will be asked to administer CHE with food.

Participants will complete monthly study visits and receive a one monthly supply of MPL-001. They will be instructed on how many drops to administer daily for the following one-month period. Participants will be asked to administer the intervention for the next month at escalating doses of 0.4-0.6 mg/kg/day then 0.6-0.8 mg/kg/day at the visit 4, and finally 0.8-1.0 mg/kg/day at visit 5. Blood samples will be drawn each month to measure the plasma concentration of CBD, THC, and its metabolites before increasing the dose, pregnancy test and liver and renal safety lab test. For all the follow-up visits, participants will be asked to provide information about PedsQL ™ Family Impact Module assessment and perception of improvement, self-directed goal attainment scaling.

**Weaning Phase (from visit 6 to visit 7)**

After the baseline phase (one month) and the treatment phase (four months), participants will start the weaning schedule, which comprises incrementally reducing the dose leading to complete discontinuation of the study product. The intervention dose will be decreased in 0.2mg/kg increments every week. The intervention will be discontinued by visit 7. If the parents, adolescents, and healthcare providers feel an improvement in chronic headache, participants will be offered a medical cannabis authorization at the end of the study.

All participants and their caregivers will be invited to complete a post-study interview (telephone) about their experiences in the trial to inform future research. Questions will be asked around their overall impression of the trial, perceived risks, benefits, how it changed during the trial, outcome importance for future studies, challenges they encountered, and how we can improve our trial. More specific questions will also be asked on the usability and usefulness of the consent form, recruiting materials, outcomes measured and the daily headache collection tool.

## Justification for Dose

Data on the pharmacokinetics related to the active constituent of Cannabis, i.e., CBD and THC, in adolescents are lacking. The CBD dose is extrapolated from safety data obtained in clinical trials in children with refractory epilepsy in the current study.[[1-7](#_heading=h.184mhaj), [118](#_heading=h.2i9l8ns)] Moreover, we made our present considerations about the dosing regimen based on the nature of our study product, namely an extract containing one of the major biologically active cannabinoids but also with pharmacologically relevant levels of other cannabinoids such as THC and cannabichromene.[[119](#_heading=h.xevivl)] CBD was found to be safe and well-tolerated in children with refractory epilepsy at a dose of 10-20mg kg/day. The suggested dose of CBD in the phase 2 study of refractory epilepsy was 10 mg/kg/day. [[1](#_heading=h.184mhaj), [4](#_heading=h.meukdy), [5](#_heading=h.36ei31r), [7](#_heading=h.45jfvxd), [113](#_heading=h.24ufcor), [118](#_heading=h.2i9l8ns)] The use of THC is associated with some risk of developing adverse effects on the central nervous system and peripheral organ system. However, these appear to be mitigated by the coadministration of CBD. THC possesses its significant pain-relieving potential at very low doses. [[120](#_heading=h.3hej1je)] The quantity of THC in our study product is 2mg per mL, with maximum THC doses only reaching 0.04mg/kg/day, which we do not expect to be associated with any adverse psychoactive reactions. In this study, the maximum dose of CBD will be less than 10 percent of the recommended dose of the CBD in the previous studies conducted in the pediatric population. We aim to keep the CBD dose as low as possible to reduce costs for families to confirm a tolerable dose and demonstrate efficacy in future clinical trials.

# STUDY POPULATION

## Inclusion Criteria

To be eligible to participate in this study, an individual must meet all of the following criteria:

1. Adolescents aged between 14-17 years of age at the time of screening.
2. Diagnosed with Chronic Migraine according to ICHD-3: headache (migraine-like or tension-type like) occurring on 15 or more days per month for more than 3 months which on at least 8 days per month have features of migraine headache. [[121](#_heading=h.1wjtbr7)]
3. Failed at least two treatment options on the grounds of safety (tolerability) and/or efficacy, including but not limited to antidepressant (tricyclic antidepressant or selective norepinephrine reuptake inhibitor), magnesium, gabapentinoids topiramate and/or non-pharmacological therapies.
4. Females who have reached menarche should have a negative pregnancy test during screening.
5. Must be willing to engage with psychology and physiotherapy throughout the trial as appropriate.

## Exclusion Criteria

An individual who meets any of the following criteria will be excluded:

1. As per the investigator judgement, the participant is not an ideal candidate due to a personal issue or medical condition that is likely to impede in the successful completion of the study
2. Participants with a history of post-concussion headache or new daily persistent headache
3. Participants with a diagnosis of medication overuse headache
4. Participants with cardiac, renal or hepatic disease (assessed by the site investigator)
5. Participants with complex regional pain syndrome-II
6. Participants with abnormal ECG findings at baseline (as determined by the investigator)
7. Participants who are on the following medications: opioids, antipsychotics, antimanic, barbiturates, benzodiazepines, muscle relaxants, sedatives, or tramadol.
8. Participants with developmental delay or impairments including autism, cerebral palsy or intellectual disability.
9. Participants with a personal or family history of schizophrenia or psychotic disorders
10. Participants who are pregnant or breast/chest-feeding or plans to become pregnant within the study period or within three months of interventional product discontinuation
11. Participants who cannot commit to using contraception and refraining from recreational cannabis use and driving throughout the study period
12. Participants with known allergy to cannabinoids and/or palm/coconut oil

